## Abstract

**Background::**

Antimicrobial photodynamic therapy (aPDT) has been used for the treatment of dental caries. Papacarie is a gel composed of papain and chloramine employed for the partial removal of carious tissue, effective against bacteria, however, some studies report that this antibacterial action is not quite so evident. The aim of this study is to evaluate the clinical effect of aPDT on infected dentin in dental caries lesion in primary teeth.

**Methods::**

Thirty-two primary molars with deep occlusal dental caries will be selected and divided in 2 groups: G1 – caries removal with a low-speed drill and G2 – application of aPDT with PapacarieMBlue. After treatment, all the teeth will be restored with glass ionomer cement and followed up clinically and radiographically, with evaluations at 3, 6, and 12 months. Dentin samples before and after treatment will be analyzed microbiologically. The data will be submitted to descriptive statistical analysis of the association between the categorical variables and both age and gender using the chi-square test and Fisher exact text. The Student *t* test and analysis of variance will be used for the comparison of mean signs and symptoms of reversible pulpitis. Pearson correlation coefficients will be calculated for the analysis of correlations among the continuous variables.

**Discussion::**

Adding methylene blue dye to the formula of PapacarieMBlue might potentiate the antimicrobial action of aPDT and work more effectively on the infected dentin combined with a conservative, minimally invasive treatment.

**Trial registration::**

NCT02734420 on 10 march 2016.

## Introduction

1

Dental caries remains a public health problem throughout the world and develops as the result of a dynamic process mediated by acid produced by cariogenic bacteria, leading to the loss of dental tissue.^[1]^ Minimal intervention combined with knowledge regarding the development of dental caries has led to major transformations in the restorative treatment paradigm, with a striking change involving the maximal preservation of sound dental tissue capable of remineralization.^[2,3]^

The partial removal of dental caries with the aim of maintaining the integrity of the pulp is currently considered the treatment of choice for deep carious lesions provided that certain diagnostic principles are respected.^[3–5]^ With minimally invasive clinical treatment using different procedures,^[6,7]^ the most superficial layer of infected dentin, which is irreversibly denatured and not capable of re-mineralization, is removed.^[5–8]^ The more internal or “affected” dentin is reversibly denatured and capable of remineralization and should be preserved.^[3,9–11]^ Thus, various aspects are important to the indication and performance of these procedures, such as the defense mechanism of the dentin-pulp complex in the occurrence of dental caries, the initial diagnosis, the differentiation of the types of dentin that compose the carious lesion, and the materials indicated for application to the remaining dentin.^[12–14]^

Papacarie^TM^ is a gel composed of papain and chloramines.^[3,15,16]^ The latter has disinfectant quality and the former is an enzyme similar to human pepsin that acts as a debriding agent that does not harm sound tissue and accelerates the healing process; papain also has bactericidal, bacteriostatic, and anti-inflammatory properties.^[17–19]^ Thus, it is associated with minimally painful treatment for caries lesions from primary teeth^[20,21]^ and exerts a positive result in bacterial reduction.^[21]^

Studies have demonstrated that antimicrobial photodynamic therapy (aPDT), have also been developed for the treatment of dental caries.^[22–27]^ The photodynamic action occurs when a photosensitizing agent absorbs photons from the light source and its electrons enter an excited singlet state.^[28]^ Different classes of chemical compounds, such as phenothiazines, phthalocyanines, and porphyrins, which have photoactive properties, have been effective in aPDT.^[23–26,28–32]^ Light must interact with the tissue in order to produce biological effect. The use of a chromophore applied to dentinal tissue has the function of absorbing light radiation, thereby increasing the interaction of the light with the tissue.^[22,23]^

Methylene blue (MB) is a widely known histological dye that has been in use for many years.^[33]^ It belongs to the phenothiazinium class of compounds. It is an amphiphatic tricyclic planar cationic molecule with 1 intrinsic quarternary nitrogen atom, and it presents phototoxic efficiency.^[34,35]^ Due to its photochemical and photobiological characteristics, widespread availability and ability to be excited with light, the aim of adding MB to the gel is to potentiate the antimicrobial action of aPDT.

## Justification

2

Studies have shown that therapeutic measures, such as aPDT, have also been developed to the treatment of dental caries.^[22–26]^ However, there are few controlled clinical trials in the literature that confirm the effectiveness of this type of therapy on caries, especially in the primary dentition.

Controlled clinical trials developed to evaluate the clinical and antimicrobial action of Papacarie^TM^ have demonstrated its effectiveness against bacteria due to its properties.^[5,6,9]^ However, some studies report that this antibacterial action is not quite so evident. Thus, knowing the effective action of aPDT on infected dentin in young permanent teeth, as reported by Guglielmi et al in 2011,^[8]^ our aim in adding the dye to its formula was to develop a conservative treatment for the removal of carious tissue combined with the possible effective action against bacterial in infected dentin of primary teeth.

The justification for the addition of the dye for subsequent aPDT is to potentiate the antimicrobial action of aPDT and work more effectively on the infected dentin combined with a conservative, minimally invasive treatment.

## Methods

3

### Objectives

3.1

#### General objectives

3.1.1

To investigate the use of aPDT on the infected dentin of primary teeth through a controlled clinical trial.

#### Specific objectives

3.1.2

1.To compare photodynamic therapy with MB and PapacarieMBlue Papacarie^TM^ with regard to microbiological, radiographic, and clinical aspects.2.To evaluate the antimicrobial effect of aPDT on infected dentin in primary teeth.3.To perform a radiographic evaluation of the remaining dentin and radiographic density at 3 evaluation times over a 12-month period.

Hypothesis (H_1_): The administration of aPDT is effective in the treatment of infected carious dentin in primary teeth.

Hypothesis (H_0_): The administration of aPDT reduces the number of viable bacteria, but is not effective in the treatment of infected carious dentin in primary teeth.

#### Trial design

3.1.3

Randomized, controlled, blind, clinical trial

#### Participants

3.1.4

Volunteers: Thirty-two teeth will be selected from male and female children (with no restrictions regarding race or ethnicity) enrolled for treatment at the pediatric clinic of the dentistry course of Nove de Julho University (São Paulo, Brazil).

#### Inclusion criteria

3.1.5

1.Adequate health with no systemic conditions;2.Adequate cooperation;3.Clinically presenting at least 1 primary molar with an acute, active caries on the dentin not surpassing 2/3 and only involving the occlusal face, with direct view and access as well as no clinical or radiographic signs of pulp involvement.

#### Exclusion criteria

3.1.6

1.Systemic adverse health condition;2.Uncooperative behavior;3.Class II, III, IV, or V carious lesion based on Black classification;4.Clinically: caries involving enamel, deficient restorations, small carious lesions on dentin with no access for manual scalers, hidden caries, sign or symptom of pulp involvement, clinical impossibility of restoration;5.Radiographically: evidence of pulp involvement, carious lesion extending beyond 2/3 of dentin.

#### Interventions

3.1.7

Group 1 – Caries removal with a low-speed drill.

1.Initial periapical and interproximal radiographs with double films;2.Prophylaxis with toothbrush and fluoride toothpaste;3.Relative isolation with lip bumper, cotton roll, and aspirator;4.Microbiological sampling with ear curette for standardization of volume of carious tissue;5.Removal of carious dentin with carbide burs and manual instruments;6.Additional microbiological sampling;7.Clinical inspection of texture of remaining dentin with an exploratory probe;8.Restoration with glass ionomer cement (Ketac Molar EasyMix – 3M ESPE);9.Clinical and radiographic follow-up.

Group 2 – Removal of carious tissue around cavity walls with dentin curette, administration of PapacarieMBlue modified with MB and aPDT.

1.Initial periapical and interproximal radiographs;2.Relative isolation with lip bumper, cotton roll, and aspirator;3.Microbiological sample with otoscope curette to standardize volume of carious tissue;4.Application on PapacarieMBlue (addition of MB) for 5 minutes as a preirradiation time to potentiate effect of aPDT; removal of carious tissue around lateral walls of the cavity with noncutting curette; no removal of carious tissue on pulp floor;5.Irradiation of dental tissue for 1 minute on a single point;6.Second microbiological sample of remaining dentin with curette;7.Clinical evaluation by inspection of texture of remaining dentin with exploratory probe;8.Restoration with glass ionomer cement (Ketac Molar EasyMIx 3M ESPE);9.Follow up;10.Radiographic control: periapical and interproximal radiographs at 3, 6, and 12 months.

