
Immediately after the removal of the carious tissue, samples of the remaining dentin will be taken with a Meyhoefer auricular n° 2 curette and the aforementioned procedures will be repeated.

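### As written, the CFU samples are not taken under matching conditions: prophylaxis precedes the first sample in Group 1 only, and two sections time the second Group 2 sample differently relative to irradiation

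*Protocol article*

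**What the plan says.** Three parts of the protocol article govern the microbiological samples.

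- **First sample (Interventions, 3.1.7).** After the initial radiographs, the Group 1 list gives "Prophylaxis with toothbrush and fluoride toothpaste" as step 2, then isolation, then the first sample. The Group 2 list opens with "1.Initial periapical and interproximal radiographs;2.Relative isolation with lip bumper, cotton roll, and aspirator;3.Microbiological sample with otoscope curette to standardize volume of carious tissue". The Microbiological evaluation section (3.1.12) adds only that this sample precedes caries removal; it does not mention brushing for either group.
- **Second sample, Group 2 (Interventions, 3.1.7).** Gel application and curettage of the lateral walls are step 4. The list then continues "5.Irradiation of dental tissue for 1 minute on a single point;6.Second microbiological sample of remaining dentin with curette".
- **Second sample, both groups (Microbiological evaluation, 3.1.12).** "Immediately after the removal of the carious tissue, samples of the remaining dentin will be taken". No exception or separate rule is given for Group 2.

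The Sample size section (3.1.8) bases its calculation on CFU, treats the samples as paired and arrives at 16 teeth per group. The second specific objective (3.1.2) is the antimicrobial effect of aPDT on infected dentin.

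**The concern.** A comparison of bacterial counts between two treatments is fair only if the samples are collected in the same way apart from the treatment. The two numbered lists otherwise run nearly in parallel, so a step that appears before the first sample in one list only reads as an instruction. Randomisation does not remove an error of this kind, because the step goes with the assigned group. Blinding the microbiological examiners does not remove it either, because it arises before the specimen reaches them.

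The second-sample wording raises a different problem. A sample taken between step 4 and step 5 in Group 2 would reflect the gel and the curettage but not the light, and so could not serve the objective that concerns aPDT. An operator working from the laboratory section and one working from the Interventions list could sample at different moments.

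**Working it through.** **Step 1. Order of events up to the first sample**

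| | Group 1 | Group 2 |
|---|---|---|
| Radiographs | step 1 | step 1 |
| Prophylaxis | step 2 | not listed |
| Isolation | step 3 | step 2 |
| First sample | step 4 | step 3 |

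The only difference in the sequence is the prophylaxis step.

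**Step 2. Order of events up to the second sample**

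| | Group 1 | Group 2 |
|---|---|---|
| Caries removal | step 5 | step 4 (lateral walls, with gel) |
| Irradiation | none | step 5 |
| Second sample in Interventions | step 6 | step 6 |
| Second sample in Microbiological evaluation | directly after removal, so after step 5 | directly after removal, so between steps 4 and 5 |

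The two sections agree for Group 1 and disagree for Group 2. The laboratory section does not mention irradiation; the earlier time follows only from combining its wording with the Group 2 step order.

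**Step 3. How a brushing effect would travel**

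Suppose, as an assumption, that brushing lowers the first Group 1 count by b on the analysis scale.
- If the analysis compares change between first and second sample, and brushing does not affect the second count, the Group 1 reduction is understated by b and the comparison shifts by b towards Group 2.
- If brushing lowers both Group 1 counts equally, b cancels in the change.
- If only second-sample counts are compared, b does not enter through the first sample.
- If brushing does not alter counts in curetted dentin, b = 0.

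The Sample size section does not say that change from the first sample was the sizing quantity, and the Statistical analysis section (3.1.17) does not specify the CFU comparison. Neither size nor direction can therefore be fixed from the text.

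**Step 4. The plan's own figure**

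The 16 teeth per group cannot be reproduced, because the expected difference and standard deviation are in figures that are not shown. The stated 1.96 and 0.84 are the correct normal quantiles for two-sided 5% and 80% power. Inverting the calculation:
- paired: (1.96 + 0.84)/√16 = 2.80/4 = 0.70 SD of the within-pair difference;
- independent groups: 2.80 × √(2/16) = 0.99 SD.

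The sample size itself is not affected by this point.

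**Step 5. Sensitivity, on assumed shifts only**

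Take 16 pairs, no true treatment effect, and a systematic shift d in SDs of the paired difference. Under the normal approximation, the two-sided rejection rate is Φ(4d − 1.96) + Φ(−4d − 1.96), where 4 = √16.

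| Assumed d | Rejection rate |
|---|---|
| 0 | 5.0% |
| 0.10 | 6.9% |
| 0.25 | 17.0% |
| 0.50 | 51.6% |

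No value of d comes from the documents. The table shows only that a trial of this size is not protected against a modest systematic shift, if there is one.

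**The case against.** The strongest reply is that both parts are loose drafting.

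- **Prophylaxis.** The Group 2 list may be abbreviated. Double film is named only in the Group 1 list, yet the Radiographic evaluation section (3.1.13) applies it to all radiographs, so a detail missing from the Group 2 list can still apply there. The Procedures section (3.1.11) also gives the other treatment to another tooth of the same child. If both teeth were treated at one visit, which is not stated, brushing could reach both.
- **Second sample.** The Interventions list is the only group-specific sequence, and it puts the sample after irradiation. The abstract agrees, with samples on either side of treatment. The article also uses removal loosely elsewhere: the section on procedure time (3.1.14) runs the clock to complete removal, although Group 2 leaves caries on the pulp floor.

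These arguments carry weight. They rule out the stronger inference that the trial will sample Group 2 before the light and measure none of its effect. They also rule out treating the brushing difference as a settled design decision with a known bias. They do not remove the point. The film detail is restored by another section, whereas nothing restores prophylaxis for Group 2. And the loosely worded sentence is the sampling instruction in the laboratory section.

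A reader might also infer a fault from the unstated sampling surface, since Group 2 walls are curetted while the floor is left. That is detail an article may leave to the full protocol, and it is not raised here.

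**Conclusion.** The point holds as two inconsistencies in how the CFU samples are specified. First, the written steps before the first sample differ by group, so the between-group CFU comparison can be biased; the amount and sign are unknown and could be zero. Second, the laboratory section and the Group 2 list conflict on whether the second sample precedes or follows irradiation. The later time is the better supported reading, but the literal earlier one would miss the light effect that the second specific objective asks about.

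The conclusion rests on the lists being followed as printed. It does not depend on any assumed brushing effect or on a change-from-baseline analysis. It is worth correcting because CFU is the variable used for the sample size and the correction is cheap. It is not evidence that the trial's results will be wrong.

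**What to change.** 1. Reconcile the Group 1 and Group 2 lists in Interventions so that the steps before the first sample are the same in both groups. If prophylaxis was always meant to apply equally, say so. This review does not propose which version of the list should stand.
2. Reconcile the second-sample sentence in Microbiological evaluation with step 6 of the Group 2 list, so that one statement places the second sample after the last active step in each group.

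No sampling site and no treatment step is prescribed. The cost is wording and, at most, a brief brushing step made the same for both groups. No extra sample is needed, and the sample size does not change.

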#### Sample size

3.1.8

The sample size will be calculated based on a previous study in the literature^[30]^ (Fig. 1), considering the expected difference and standard deviation and weighting colony forming units (CFU) of bacteria. For the statistical calculation, paired samples were considered, with *α* = 1.96 (5%); *β* = 0.84 (20%), and an 80% test power. The minimum number in this clinical trial was determined to be 16 teeth per group (Fig. 2).

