#### Procedures

3.1.11

Training and calibration of operator and examiner: All treatments will be performed by a single examiner who will undergo a training and calibration exercise in the initial phase of the study involving teeth randomly allocated to 2 groups. The operator will perform the treatment and a previously trained examiner will perform a clinical evaluation of the removal of carious tissue. The examiner will be unaware of the technique applied to the teeth (blind study). The previously trained examiner will evaluate all cavities after the respective interventions and will test the hardness of the remaining dentin. For carious tissue to be considered removed, there must be agreement between the operator and the examiner. This pilot study will be conducted to determine interexaminer agreement regarding the clinical and radiographic evaluations by examiners having undergone a calibration exercise with the calculation of Kappa coefficients. Interexaminer agreement must be greater than 85% (*K* > 0.85).

Randomization: The type of treatment will be determined based on the identification of the lottery stone:

Number 1 – Traditional caries removal with a low-speed drill (Group 1).

Number 2 – Removal of carious tissue around cavity walls with dentin curette, aPDT with PapacarieMBlue administration of PapacarieMBlue modified with MB followed by aPDT (Group 2).

Next, the individual and tooth will receive the previously determined treatment. Likewise, another tooth in the same individual will receive the treatment that was not determined previously.

Blinding: The clinical evaluations of the carious tissue removal, as well as the microbiological and radiographic analyses, will be performed by examiners blinded to the treatments performed on each tooth.

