#### Statistical analysis

3.1.17

The data will be analyzed statistically employing different tests and considering a 5% level of significance. The results will be submitted to descriptive analysis for the association of categorical variables in age and gender using the chi-square test and Fisher exact test. The Student *t* test and analysis of variance will be used for the comparison of means of the signs and symptoms of reversible pulpitis. Pearson correlation coefficients will be calculated to determine correlations among the continuous variables.

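### If the 16 teeth per group come straight from the normal quantiles 1.96 and 0.84, a paired t test on CFU has about 74.5% to 77.1% power, not the stated 80%

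*Protocol article*

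**What the plan says.** Section 3.1.8 (Sample size) bases the calculation on an earlier study, "considering the expected difference and standard deviation and weighting colony forming units (CFU) of bacteria". It then gives the constants: "For the statistical calculation, paired samples were considered, with *α* = 1.96 (5%); *β* = 0.84 (20%), and an 80% test power". The result is: "The minimum number in this clinical trial was determined to be 16 teeth per group". The formula and the planning values are referred to Figures 1 and 2, which are not reproduced in the text at hand.

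Pairing is also described in 3.1.11 (Procedures), where "another tooth in the same individual will receive the treatment that was not determined previously".

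Section 3.1.17 (Statistical analysis) states: "The Student *t* test and analysis of variance will be used for the comparison of means". That sentence goes on to limit these tests to signs and symptoms of reversible pulpitis. The article names no test for CFU.

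**The concern.** The values 1.96 and 0.84 are standard normal quantiles. A sample size built on them is right for a test in which the SD of the paired difference is known. In a trial of 16 pairs that SD is estimated from the same 16 differences. The reference distribution is then t with 15 degrees of freedom, whose two-sided 5% critical value is 2.131 rather than 1.96. In large trials the difference is negligible, but at 16 pairs it is not.

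This is separate from the question of whether the analysis respects the pairing. It would arise even with perfect pairing and a correctly paired test. What is at stake is how a null result is read: a non-significant CFU comparison would be taken to come from a trial with 20% type II error, when the true figure may be nearer one in four.

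**Working it through.** **Inputs from the article (3.1.8):** paired samples; 1.96 for 5%, hence two-sided; 0.84 for 80% power; 16 teeth per group, taken as 16 pairs.

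**Assumptions:** the formula is n = ((1.96 + 0.84) × SD/d)², rounded up, with no small-sample addition. Here d is the expected mean paired difference and SD the standard deviation of the paired differences. All 16 pairs are complete and the differences are normal.

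**Step 1: the plan's own figure.** The 16 cannot be reproduced directly, because d and SD are in the figures. The constants agree with their labels: 2 × (1 − Φ(1.96)) = 0.0500 and Φ(0.84) = 0.7995. Solving the formula backwards gives d/SD = 2.80/√n:
- n exactly 16: 2.80/4 = 0.700
- n = 15.5 before rounding: 2.80/√15.5 = 0.711
- n just above 15 before rounding: 2.80/√15 = 0.723

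The known-SD power at 16 pairs is Φ(4 × d/SD − 1.96). At 0.700 this is Φ(0.84) = 79.95%, and at 0.723 it is 82.4%. Both agree with the printed 80%, but the check is circular because d/SD was derived from the result.

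**Step 2: power with the SD estimated.** For a paired t test on 16 differences, degrees of freedom = 15, critical value = 2.131 and noncentrality = (d/SD) × √16.

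| d/SD | noncentrality | power | shortfall from 80% |
|---|---|---|---|
| 0.700 | 2.80 | 74.5% | 5.5 points |
| 0.711 | 2.84 | 75.8% | 4.2 points |
| 0.723 | 2.89 | 77.1% | 2.9 points |

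Type II error is therefore 22.9% to 25.5% instead of 20%.

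**Step 3: what 80% would need.**
- At 16 pairs: d/SD = 0.749.
- At d/SD = 0.700: 18 pairs give 79.9% and 19 give 82.3%.
- At d/SD = 0.723: 17 pairs give 79.9% and 18 give 82.4%.

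The approximation is thus worth about 2 to 3 pairs.

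**Step 4: other readings of the unseen formula.**
- A small-sample addition was already made. At d/SD = 0.749 the normal formula gives (2.80/0.749)² = 13.96, about 14. Raising this to 16 gives 80% power for the paired t test, and nothing is overstated.
- The two-sample formula was used with 16 per group. Then d/SD = 2.80 × √(2/n) = 0.990 to 1.022, with SD now that of a single measurement, and an unpaired t test on 30 degrees of freedom has 77.3% to 79.9% power.

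**The case against.** The strongest objection is that the formula and planning values cannot be seen. A reader might infer that the power is overstated whatever the figures contain. The documents do not support that. The range of 74.5% to 77.1% covers every rounding within one assumed formula only, and a start from about 14 pairs with 2 added would deliver the stated 80%. What remains is that the text lists normal constants, then a minimum of 16, and mentions no correction. The uncorrected paired formula is the natural reading, but it is an inference.

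A reader might also infer that the plan commits CFU to a t test and so contradicts its own sizing. It does not: the t test and ANOVA are named only for signs and symptoms of reversible pulpitis, and the CFU test may be set out in a fuller document. This removes the claim of a contradiction but not the point itself. The sizing rests on an expected mean difference and its SD, and any comparison of mean paired differences must estimate that SD from the 16 pairs.

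A third tempting inference is that enrolment equals the minimum, so that no margin absorbs the shortfall. The Abstract and 3.1.4 (Participants) do give 32 teeth, but 3.1.13 (Radiographic evaluation) refers to 48 teeth in 48 patients. With that conflict open, neither the margin nor the number of complete pairs is settled.

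Finally, the effect is modest and the approximation is a textbook one, openly disclosed. An SD lower than planned by 1 − 0.723/0.749 = 3.5% to 1 − 0.700/0.749 = 6.5% would cancel it, and a planning value from one earlier study could easily be wrong by that much. This is fair. It limits the weight of the point, but it is no reason to leave a printed power figure that the stated method does not deliver.

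**Conclusion.** The point holds conditionally. If 16 is the rounded-up output of the paired normal formula and CFU is compared through mean paired differences with an estimated SD, power is about 74.5% to 77.1%, which is 2.9 to 5.5 points below the stated 80%. This rests on a two-sided 5% level, 16 complete pairs, normally distributed differences and no small-sample correction. It is not established that the planning calculation omitted such a correction. The consequence is limited: the printed power needs restating or a short justification, and the design need not change.

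**What to change.** Keep 16 teeth per group. In 3.1.8, recompute power from the noncentral t distribution with 15 degrees of freedom, using the trial's own expected difference and SD from the figures. Then do one of the following:
- replace the 80% with the recomputed value, which is about 75% to 77% under the assumption above; or
- keep 80% and state the detectable difference as about 0.75 SD of the within-pair difference.

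If the 16 already includes a small-sample correction, say so in one clause, and no other change is needed.

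The cost is one sentence and possibly a slightly less favourable stated figure. No added enrolment is called for.

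### Unit and pairing are inconsistent across the protocol (paired sizing, within-child allocation, one-molar eligibility, 48 teeth in 48 patients), so the stated 80% power is not assured

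*Protocol article*

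**What the plan says.** - **Sample size (3.1.8):** the calculation was done "considering the expected difference and standard deviation and weighting colony forming units (CFU) of bacteria", with z values 1.96 and 0.84. It adds "For the statistical calculation, paired samples were considered", and "The minimum number in this clinical trial was determined to be 16 teeth per group". The difference and SD come from a cited study and appear only in figures that are not shown. The text does not say whether a pair is two teeth in one child or two samples from one tooth.
- **Participants (3.1.4):** "Thirty-two teeth will be selected from male and female children". The number of children is not given.
- **Procedures, Randomization (3.1.11):** after the draw for the first tooth, "another tooth in the same individual will receive the treatment that was not determined previously". This is within-child allocation.
- **Inclusion criteria (3.1.5):** "Clinically presenting at least 1 primary molar with an acute, active caries on the dentin". One eligible molar is enough.
- **Radiographic evaluation (3.1.13):** the density analysis is described for 48 teeth in 48 patients, which is one tooth per child. Optical density is to be analysed with a mixed-effects model.
- **Statistical analysis (3.1.17):** chi-square and Fisher tests are for "association of categorical variables in age and gender using the chi-square test and Fisher exact test". Student t and ANOVA are for signs and symptoms of reversible pulpitis, and Pearson coefficients are for correlations among continuous variables. Pairing is not mentioned and no test is assigned to CFU.

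**The concern.** The sizing, allocation, eligibility and analysis sections do not describe one design. A child with a single eligible molar satisfies the inclusion criterion, but the allocation rule cannot be carried out for that child because there is no second tooth. One tooth in each of 48 patients contradicts both the within-child allocation and the total of 32 teeth.

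This bears on power. A paired calculation uses the SD of the within-pair difference, which is smaller than the SD for independent teeth when teeth in the same mouth are positively correlated. If pairs are missing, or are analysed as if independent, the same 16 per group buys less precision. If the pair in the calculation was before and after in one tooth, the calculation answers whether one group changes, not whether the two treatments differ.

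**Working it through.** **Inputs.** From the sample size section: two-sided 5% (z = 1.96), 80% power (z = 0.84), 16 per group, paired. Not in the text: the difference, the SD and the within-child correlation rho. Rho is assumed over 0 to 0.7.

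**1. Can 16 be reproduced?** No. The formula n = ((1.96 + 0.84) × SD_diff / difference)² needs the two missing inputs. Inverting it, and assuming that 16 is the number of pairs it returned:
- 2.80 / √16 = 0.70 SD of the paired difference;
- 2.80 / √15 = 0.72, the upper end if n was rounded up from just above 15.

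**2. 16 complete pairs, paired t test** (noncentral t, 15 degrees of freedom):
- effect 0.70: power 74.5%;
- effect 0.72: power 77.1%;
- effect 0.75: power 80.1%.

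At 0.70, 18 pairs give 79.9%, so strictly 19 are needed. The gap from 80% is the usual normal-versus-t difference in a small sample.

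**3. Pairing ignored or absent.** For tooth-level SD 1, SD_diff = √(2(1 − rho)), so the between-treatment difference is d = 0.70 × √(2(1 − rho)). Two cases with 16 v 16 teeth: an unpaired t test applied to 16 true pairs (simulation), and an unpaired t test on teeth from different children (noncentral t, 30 degrees of freedom).

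| rho (assumed) | d | True pairs, unpaired test: power | Its type I error | Teeth from different children: power |
|---|---|---|---|---|
| 0 | 0.99 | 77% | 5.0% | 77% |
| 0.3 | 0.83 | 64% | 2.1% | 62% |
| 0.5 | 0.70 | 48% | 0.8% | 48% |
| 0.7 | 0.54 | 22% | 0.1% | 32% |

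**4. Some pairs missing, analysis that respects pairing.** With m pairs and 16 − m single teeth per group, the information is m / (2(1 − rho)) + (16 − m) / 2, and approximate power is Φ(d × √information − 1.96). For m = 8:
- rho 0.3: information 8/1.4 + 4 = 9.71, power 73%;
- rho 0.5: information 8/1 + 4 = 12, power 68%.

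These are normal approximations, to be compared with 80% for 16 pairs on the same scale. The true number of single-molar children is unknown.

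**5. If paired meant before and after in one tooth.** Comparing change between 16 and 16 teeth at a standardised effect of 0.70 is a two-sample t test with noncentrality 0.70 × √8 = 1.98. Its power is about 48%. The normal approximation gives 51% and would need 32 per group for 80%.

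**The case against.** The strongest reply is that nothing in the text commits the trial to a wrong analysis or shows that it is underpowered. Most of that stands, and it rules out two readings that a reader might infer.

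- **That the stated tests are for independent groups.** The documents do not say so. Student t and ANOVA both have paired forms, and neither is specified as unpaired. They are tied to pulpitis signs and symptoms, not to CFU. Chi-square and Fisher are stated for associations with age and gender, not as treatment comparisons. Optical density is given a mixed-effects model, which can carry a child effect. The exact CFU test may sit in an analysis plan that is not shown.
- **That the 80% is not delivered, or that true power is 75%.** This cannot be shown. The effect of 0.70 is inferred from n = 16. At 0.75, 16 pairs give 80.1% by t test. Rho is assumed, and at rho = 0 ignoring the pairing costs nothing. Where rho is above 0, the unpaired test errs on the conservative side for type I error.

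It is also fair that asking for at least one molar does not exclude children with two, so the number of broken pairs could be small.

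None of this removes the contradiction. One-molar eligibility, within-child allocation, 32 teeth, and 48 teeth in 48 patients cannot all describe the same trial. That is a conflict between statements, not detail left to another document. The before-and-after reading of paired does not protect the between-treatment comparison either.

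**Conclusion.** The point holds as an inconsistency of unit and pairing across eligibility, sample size, allocation, radiographic evaluation and statistical analysis. Its consequence is that 80% power is not assured. It depends on obtaining about 16 complete within-child pairs and analysing CFU as paired, and the document secures neither.

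The size is conditional. If 16 is the normal-approximation result, complete pairs with a paired t test give about 75% to 77%, a small shortfall. The larger potential loss is from ignoring the pairing: 64% at rho 0.3, 48% at 0.5 and 22% at 0.7, with none at rho 0. On the before-and-after reading, the treatment comparison has about 48% at the same standardised effect. None of these figures should be written into the protocol as fact, because the difference, SD and rho are not in the text.

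**What to change.** 1. Choose one design and state it under Trial design. Either require at least two eligible primary molars per child and call the design split-mouth (16 children, 32 teeth), or keep single-molar children and declare a mixed paired and unpaired design with its lower power.
2. Reconcile the 48 teeth in 48 patients with that choice.
3. Say in the sample size section what a pair is. Recompute power with the t distribution from the difference and SD actually used, and restate it for the between-treatment comparison of CFU.
4. Name the CFU analysis. For CFU and other continuous treatment comparisons, use a paired test or a mixed model with child as a random effect (the mixed model if single-molar children are kept). For binary treatment comparisons, use exact McNemar or conditional logistic regression.

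**Cost.** This is mainly wording and one recalculation. Under the split-mouth option, children with a single eligible molar can no longer be recruited. The restated power may be slightly less favourable than 80%. If the pair turns out to have been before and after in one tooth, the recalculation could show a larger gap.
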